### **Suspected Unexpected Serious Adverse Reactions (SUSARs)**

A SUSAR is an unexpected adverse drug reaction that is at least possibly related to the IMP or the study procedure. The Sponsor-Investigator receives the SAE evaluation about seriousness and causality from the Study Investigator. The Sponsor-Investigator evaluates any SAE that has been reported regarding expectedness. If the event is at least possibly related to the investigational product and is both serious and unexpected, it is classified as a SUSAR.

### **Assessment of Severity of (Serious) Adverse Events and other safety related events**

Assessment of severity of events will be performed on the basis of the DAIDS Table for Grading the Severity of Adult and Pediatric Adverse events (version 2.0, November 2014) (95).

## **10.1.2. Reporting of (Serious) Adverse Events and other safety related events**

### **Reporting of SAEs**

All SAEs must be reported immediately and within a maximum of 24 hours to the Sponsor-Investigator of the study. The Sponsor-Investigator will evaluate the expectedness of the SAE.

SAEs resulting in death are reported to the leading Ethics Committee by the Sponsor-Investigator within 7 days.

### **Reporting of SUSARs**

A SUSAR must be reported to the leading Ethics Committee via the Sponsor-Investigator within 7 days if the event is fatal, or within 15 days for all other events.

The Sponsor-Investigator must inform all investigators participating in the clinical study of the occurrence of a SUSAR within the same time frame.

### **Reporting of Safety Signals**

All suspected new risks and relevant new aspects of known adverse reactions that require safety-related measures, i.e. so called safety signals, must be reported to the Sponsor-Investigator within 24 hours. The Sponsor-Investigator must report the safety signals within 7 days to the leading Ethics Committee and all investigators participating in the clinical study.

### **Reporting and Handling of Pregnancies**

Pregnant women are not eligible for the study. A pregnancy occurring during the study does not lead to a study withdrawn. Any pregnancy occurring during the treatment phase of the study and within 30 days after discontinuation of study medication will be reported to the Sponsor-Investigator within 24

hours. The course and outcome of the pregnancy will be followed up carefully, and any abnormal outcome regarding the mother or the child will be documented and reported to the Sponsor-Investigator. Pregnancies and their outcomes should be followed until resolution or stabilisation. Participants with ongoing pregnancy at week 48 or study discontinuation visit will be further followed up until pregnancy resolution. In case of newborn health problem, the duration of the follow-up can be extended.

#### **Periodic reporting of safety**

An annual safety report will be submitted once a year to the leading Ethics Committee by the Sponsor-Investigator. This annual safety report will contain information from all study sites. The Sponsor-Investigator will prepare the annual safety report and distribute it to the participating Investigators.

#### **10.1.3 Follow up of (Serious) Adverse Events and other safety related events**

Participants with ongoing AE, SAEs, SUSARs or pregnancy at week 48 or at study discontinuation visit will be further followed until either final outcome or 6 weeks (+/- 5 days) after the last patient last visit. Ongoing pregnancies at 48 week visit or at study discontinuation visit will be further followed-up until pregnancy resolution. Extension of this duration can be proposed for event of particular interest for the study. Follow up may include but is not limited to physical examination, laboratory tests, vital signs, telephone calls. Outcomes and resolution of events will be recorded in the Case Report Forms. In case of lost to follow up, efforts will be made to contact the patient or to ascertain the vital status of the participant.

## 11. STATISTICAL METHODS

### 11.1 Hypotheses

- HA1: DTG + FTC maintenance dual therapy is non-inferior to cART in maintaining plasma HIV viral load <100 copies/ml throughout 48 weeks in virologically suppressed patients.
- HO1 (tested): DTG + FTC maintenance dual therapy is inferior to cART by 12% in maintaining plasma HIV viral load <100 copies/ml throughout 48 weeks in virologically suppressed patients.
- HA2: Patient-centered monitoring reduces health-costs compared to standard monitoring.
- HO2 (tested): Patient-centered monitoring does not reduce health-costs compared to standard monitoring.

### 11.2 Determination of Sample Size

The first sample size calculation was based on the primary outcome for the comparison between DTG + FTC dual therapy and standard cART, i.e. the comparison between the proportions of patients in the two arms maintaining virologic suppression, using a two-sample proportion test (96). The following assumptions were made:

- Power 80%
- Significance level 0.025 (one-sided Z test of non-inferiority)
- 97% of patients with conventional cART will be virologically suppressed at week 48 (<100 copies/ml)
- 94% of patients on DTG + FTC dual therapy will be virologically suppressed at week 48 (<100 copies/ml)
- Non-inferiority margin of 12% (as in previous non-inferiority trials)(97-104). We chose 12% noninferiority margin because there is no difference in terms of resistance acquisition between 10% and 22% virological failure.

Sample size of 83 patients in each group (total sample size, 166 patients) to achieve 80% power to detect a non-inferiority margin difference between the group proportions of -0.12 was calculated. The power was computed for the case when the actual cART group proportion is 97% and the actual DTG + FTC dual therapy group proportion is 94%. To allow for at least 10% loss to follow-up and also for the randomisation in two steps in this 1:1:1:1 trial, we will aim to recruit **a total of 184 patients**.

The second sample size calculation was based on the primary outcome for the comparison between simplified monitoring and standard monitoring, i.e. the comparison between mean direct costs in the two arms (105). The following assumptions were made:

- Significance level 0.05 (two-sided t-test)
- Direct costs are CHF 25,000 per year (standard deviation (SD) CHF 8,000) with conventional monitoring
- SDs are equal in the two groups (CHF 8,000)

With sample sizes of 92 patients in each group, we will have approximately 55% power to detect a 10% difference in costs, and 99% power to detect a 25% difference in costs. We will also have substantial power to detect small-to-moderate differences in many of the secondary outcomes, e.g. changes in CD4 cell counts or health-related quality of life. The exceptions are rare outcomes such as adverse events, resistance or clinical complications for which the statistical power to detect differences will be low.

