| Statistical Considerations: | 
DTG + FTC dual therapy is expected to be non- inferior to standard-of-care using a 12% non-inferiority margin assuming that 92% of patients are virologically suppressed at week 48 in the two comparison arms.
 
We will evaluate the proportion of patients with viral suppression at week 48 in each arm, and compute a Mantel-Haenszel risk difference (DTG+FTC minus cART) stratified by monitoring type with a two-sided 95% confidence interval. If the lower confidence limit is higher than -12% we will conclude non-inferiority. If the lower confidence limit is below -12% we will conclude that DTG + FTC is potentially inferior to cART. Per protocol (PP) and intention-to-treat (ITT) analyses will be performed. Exclusion criteria for PP will be: patients who discontinue treatment prematurely for reasons other than death, patients with a treatment adherence of less than 80%, or those who do not have HIV-1 RNA results available at week 48. For ITT analysis, all randomized patients will be analysed in the allocated group regardless of any protocol violations.
 |
| GCP Statement:              | 
This study will be conducted in compliance with the protocol, the current version of the Declaration of Helsinki, the ICH-GCP or ISO EN 14155 (as far as applicable) as well as all national legal and regulatory requirements.
                                                                                                                                                                                                                                                                                                                                                                                                                                                                                                                                                                                                                                                                                                                                                                                                                                                                          |

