## **11.4 Planned Analyses**

### **11.4.1 Datasets to be Analysed, Analysis Populations**

As recommended by the CONSORT statement (106), two analysis sets will be performed: per-protocol (PP) and intention-to-treat (ITT).

For PP analysis, we will exclude patients for the following reasons: patients who discontinue treatment prematurely (< 47 weeks), unless virological failure occurred before, patients with a treatment adherence of less than 80% while on treatment, those who do not have HIV-1 RNA results at week 48 (+/-21 days), unless virological failure occurred before, or patients with major protocol deviation(s) (i.e. any failure to obtain informed consent, violation of any inclusion criteria, not receiving the allocated treatment or monitoring). Per-protocol and intention-to-treat analyses should reach the same conclusion to consider DTG + FTC as non-inferior to standard treatment.

For ITT analysis, all randomized patients will be analysed in the allocated group regardless of any protocol violations.

All drop outs will be described and reasons for their discontinuation will be given where possible.

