### **11.5 Handling of missing data and drop-outs**

The following strategies will be used to replace missing values at the final study timepoint. If HIV-RNA is available at week 36, the value at time 36 will be considered (last observation carried forward). If no data is available at weeks 36 and 48, we will consider these patients as failures. The same approach will be considered for secondary outcomes. For continuous outcomes, we will exclude patients from the analysis if no data is available at weeks 36 and 48. In the snapshot analysis, patients with missing outcome in the time snapshot window will be considered as failures. Sensitivity analyses will be performed to determine whether the conclusions are sensitive to assumptions about the missing-data mechanism. We will compare patient characteristics between the two groups having or not missing data in order to assess their similarity. If differences are outlined, missing data would be considered not at random and some bias in the estimation of treatment effect would be suspected. If not, we will consider the complete case analysis as valid to estimate the noninferiority of DTG+FTC compared to standard treatment.

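### The stated 80% power describes an analysis with losses removed, not the rule that ITT and per-protocol must both show non-inferiority with some losses counted as failures; the synopsis also gives different planning rates

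*Protocol*

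**What the plan says.** Section 11.2 (Determination of Sample Size) aims for 80% power in a one-sided test at level 0.025 with a 12-point margin. Its control assumption is "97% of patients with conventional cART will be virologically suppressed at week 48 (<100 copies/ml"); for the dual-therapy arm it expects a rate three points lower, 94%. It arrives at 83 per group, 166 in total, and raises this to 184 with the explanation "To allow for at least 10% loss to follow-up and also for the randomisation in two steps in this 1:1:1:1 trial".

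Section 11.4.1 defines ITT as all randomised patients in their allocated group, and sets the condition for the claim: "Per-protocol and intention-to-treat analyses should reach the same conclusion to consider DTG + FTC as non-inferior to standard treatment".

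Section 11.5 replaces a missing week-48 HIV-RNA by the week-36 value where there is one. Otherwise: "If no data is available at weeks 36 and 48, we will consider these patients as failures".

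The synopsis (Statistical Considerations) uses the same 12% margin and 92 patients per group, but is planned "assuming that 92% of patients are virologically suppressed at week 48 in the two comparison arms".

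**The concern.** Dividing an evaluable sample by one minus the loss rate restores power only if lost patients drop out of the denominator. In this protocol's ITT analysis they do not. Those without a week-36 or week-48 value stay in and pull both success rates down from the planning values towards the middle of the scale, where the variance of a proportion is larger. Because the claim needs both analyses to succeed, the weaker one limits it and their joint power is lower than either.

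Two things are at stake. First, the funder, the ethics committee and the data monitoring board are given 80% as the chance of reaching the first primary conclusion, and that figure belongs to a different analysis. Second, section 11.4.2 reads a lower confidence limit below -12% as DTG + FTC being potentially inferior, so a shortfall caused by losses could be read as a drug effect.

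The synopsis rates add a further ambiguity: one text assumes a true 3-point deficit and the other assumes none, for the same trial.

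**Working it through.** **Inputs.** Section 11.2: one-sided 0.025, 80% power, 97% v 94%, margin 0.12, at least 10% loss, 184 recruited (92 per arm). Section 11.5: the carry-forward and failure rules. Section 11.4.1: ITT and per-protocol must agree.

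**1. The plan's own figure.** With unpooled variance,
n = (0.97×0.03 + 0.94×0.06) × (1.960 + 0.842)² / (0.12 − 0.03)² = 82.9, so 83 per arm. Power at 83 is 80.1%. Inflation: 166/0.90 = 184.4, against 184 stated. The arithmetic reproduces and confirms that losses are treated as removed.

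**2. ITT power under section 11.5.** Let L be the share of randomised patients who become failures through loss. Assume L is equal in both arms and unrelated to virological outcome. The rates become 0.97(1−L) and 0.94(1−L), and

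power = Φ( (0.12 − difference)/SE − 1.96 ), SE = √[(pc(1−pc) + pt(1−pt))/92].

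- L = 0: SE = 0.0305; 0.09/0.0305 − 1.96 = 0.99; power 84%.
- L = 10%: rates 87.3% and 84.6%; SE = 0.0512; 0.093/0.0512 − 1.96 = −0.14; power 44%.
- Power crosses 80% at L of about 0.6%.

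**3. Joint power.** I simulated 200,000 trials per row: 92 per arm, 10% loss, Wald 95% interval, unstratified. Per-protocol removes the lost patients and nobody else. ITT counts a given share of losses as failures and carries the rest forward with the arm's own success rate.

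| Share of losses counted as failures | L | ITT power, formula | ITT power, simulated | Joint ITT and per-protocol |
|---|---|---|---|---|
| none | 0% | 84% | 82% | 76% |
| a quarter | 2.5% | 68% | 69% | 65% |
| half | 5% | 57% | 58–59% | 55% |
| three quarters | 7.5% | 50% | 51% | 48% |
| all | 10% | 44% | 45% | 43% |

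An exact binomial calculation gives 46% for ITT in the last row. Per-protocol power alone was about 78% in every row of the simulation. The 76% in the first row is therefore the cost of requiring both analyses and owes nothing to failure imputation; the fall below it is due to the failure rule.

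**4. Synopsis rates.** At 92% in both arms, n = (2×0.92×0.08) × (1.960 + 0.842)² / 0.12² = 80.2, so 81 per arm, and power at 92 per arm is 85%. With all 10% of patients counted as failures the rates are 82.8%, ITT power is 58% and joint power is 56%. With no loss a failure, joint power is about 80%.

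**The case against.** **Not every loss is a failure.** This is correct. A patient with a week-36 value is carried forward. A reader might infer from section 11.5 that all of the 10% allowed for become failures and that the trial therefore has 44% power. The documents do not support that. They do not say when losses occur, so 44% is only the lower end of a range. Stopping study drug is not loss either: sections 3.7 and 7.4 generally keep such patients under follow-up to week 48.

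**Section 11.5 also mentions a complete-case analysis**, considered valid if patients with and without missing data look alike. At 83 per arm that has the stated 80%. But it appears as part of the sensitivity assessment, and it replaces neither the ITT failure rule nor the requirement that both sets agree.

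**The planning rates might already count losses as failures.** Then ITT power at 92 per arm would be 84%. Section 11.2 does not say so, and its separate allowance of at least 10% points the other way: 97% success cannot coexist with 10% of patients failing through loss.

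**Losses may overlap with patients who would fail anyway.** This stands. ITT power would then be higher than shown, which is why independence is stated as an assumption.

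**One cannot simply relabel the 80% as per-protocol power.** This also stands. Section 11.4.1 excludes more than losses: adherence below 80%, stopping before 47 weeks, no week-48 result, and major deviations. If 15% were excluded (78 per arm, an assumption) power would be 77.6%; at 20% (74 per arm) it would be 75.4%.

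**The consequences are limited.** Version 5.1 is dated July 2019, after the planned end of the 48-week phase in May 2019. Restating power changes no estimate, interval or error rate, and requiring both sets makes a false claim less likely, not more. That bounds the harm, but the figure is still wrong for the rule it accompanies.

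**Conclusion.** The point holds as an internal inconsistency. The sample-size arithmetic in section 11.2 is correct for about 83 evaluable patients per arm with losses removed; it does not describe the decision rule in sections 11.4.1 and 11.5.

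At the plan's own 97%/94% and 10% loss, joint power lies between about 76% and 43%, depending on the share of losses counted as failures, and does not reach 80% anywhere in that range. ITT power alone stays at 80% or above only if no more than about 0.6% of randomised patients become failures through loss, that is, if about 94% of a 10% loss have a week-36 value. These figures assume equal loss in both arms, independence from virological outcome, and per-protocol exclusions limited to the losses.

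The synopsis contradiction is real but separate. A reader might infer that 92%/92% weakens the trial; it does not, since it needs two fewer patients per arm than 97%/94%. Nor does any of this show that more patients should have been enrolled or that the type I error is affected.

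**What to change.** 1. In section 11.2, state that 80% applies to an analysis of about 83 evaluable patients per arm with losses removed, and that it describes the per-protocol set only if total per-protocol exclusions stay near 10%.
2. Add ITT power and joint ITT and per-protocol power under the section 11.5 rule, as a range over the share of losses counted as failures, with the assumptions named.
3. Use one set of planning rates in section 11.2 and the synopsis, and say whether they already count losses as failures. If they do, explain what the separate 10% allowance is for.

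The cost is a few sentences and a less favourable power figure. Enrolment, analysis sets, margin and decision rule stay as they are.

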### 11.3 Statistical criteria of termination of trial

This is an open label study. The laboratory results that define treatment failure (HIV-RNA) of all participants included will be available within a week to the investigators. A detailed report including a summary of Serious Adverse Events, grade 3/4 Adverse Events, laboratory toxicities as well as virological failures, pregnancies and safety signals will be sent to the DSMB on a 6-monthly basis.

To protect the safety of the study participants, a safety interim analysis on the first 100 patients randomized will be done once reached the end of the time window for their 24 weeks study visit. The following data will be reviewed:

Safety data:

- Participant recruitment, accrual, retention and withdrawal information
- Adverse events (AEs) and serious adverse events (SAEs)
- Pregnancies
- Laboratory values
- Additional virological tests performed outside study schedule
- Any other safety-supporting data requested by the DSMB

Efficacy data:

- HIV-RNA data (primary endpoint measure)
- Genotype resistance test data (secondary endpoint)

We will also convene the DSMB in the following situations:

- (1) if > 2 patients experienced virological failure and a new resistances on DTG + FTC dual therapy before the planned interim safety analysis is done;
- (2) if new published or unpublished data show any major inconvenience of testing a DTG + FTC dual therapy arm.

The DSMB will then give recommendations regarding the continuation, modification or termination of the trial.

Stopping rules:

The DSMB may recommend stopping the trial for the following reasons:

- The data show a significantly increased risk of serious adverse events in one of the study groups;
- On the basis of a positive efficacy result only when the data are truly compelling and the risk of a false positive conclusion is acceptably low. The trial will only be stopped for positive efficacy if a strong statistically and clinically significant difference in virological success is seen between treatment arms;
- If interim data suggest that the simplified treatment/monitoring arm under study is of no benefit (trend indicating clear inferiority of the simplified treatment/monitoring arm), or that accrual rates are too low and/or that noncompliance is too great to provide adequate power for identifying the specified benefit, the DSMB may consider whether continuation of the study is futile and may recommend termination on this basis;
- It becomes clear that successful completion of the study is not feasible (e.g. there is an excess of patient dropout, missing data, lack of recruitment etc).

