### 3.4 Clinical Evidence to Date

#### ***Dolutegravir efficacy data in maintenance monotherapy***

DTG monotherapy as maintenance treatment in an ART experienced population was proved to be feasible, with a high rate of effectiveness over 24 weeks in three observational studies (49, 72, 73). *Katlama et al* enrolled 28 patients virologically controlled for 6.6 years with a median nadir CD4 count of 215 cells/mm^3. The proportion of patients with viral load <50 copies/ml at week 24 was 89% (25/28 patients). Three virological failures were reported: all occurred in patients previously exposed to first generation integrase inhibitors, and patients developed signature mutations for integrase inhibitors at week 24. Patients were however switched back to conventional triple ART regimen with virological success. The study by *Rojas et al* included 33 patients, virologically controlled for 8 years and with a mean nadir CD4 count of 229 cells/mm^3 (SD ±125); 97% of patients remained with an undetectable viral load at 24 weeks. One patient, previously failing on raltegravir, demonstrated virological failure with HIV-DNA genotypic resistance test showing a signature mutation for integrase inhibitor at week 24. *Oldenbuettel et al* enrolled 31 patients virologically suppressed for 24 weeks. One patient discontinued for adverse event (ongoing cough) and one presented with virological failure at week 24. This latest patient continued on DTG monotherapy for five more weeks; the genotypic resistance test at that time showed major INSTI mutations (73).

However, an academic-driven randomized controlled trial of DTG mono-maintenance therapy (the DOMONO trial - NCT02401828) in which 104 HIV virologically suppressed patients were enrolled to an immediate or delayed (at week 24) switch to DTG monotherapy and followed throughout 48 weeks from the date of switch, was prematurely stopped because of virological failure in 10% of patients (74, 75). While DTG monotherapy was non-inferior to cART at week 24, most of virological failures occurred after week 24 and led to INSTI-associated resistance mutations in three patients.

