### **9.3.6. Week 24 ( $\pm 7$ days) at SHCS center**

*Clinical assessments:*

- Adherence session by the study nurse;
- Recording/update of concomitant medications;
- Adverse event recording;
- Physical examination and vital signs;
- Study drug distribution and return (DTG + FTC or standard cART) according to site standard practice;
- Patient's monitoring satisfaction (possibility to change patient-centered monitoring options).

*Laboratory assessments:*

- HIV-1 RNA in plasma;
- Plasma sample storage;
- Dolutegravir and emtricitabine plasma concentration if HIV-1 RNA measurement  $\geq 100$  copies/ml in plasma
- Genotypic resistance test if 2 consecutive HIV-1 RNA measurements  $\geq 100$  copies/ml in plasma;
- Pharmacogenetic analyses if 2 consecutive HIV-1 RNA measurements  $\geq 100$  copies/ml in plasma only for patients included in the SHCS and who have signed a consent form for genetic studies;
- CD4 count, full blood count, safety serum chemistry (CK, creatinine, ASAT/ALAT, gamma-GT, alkaline phosphatases, glucose and lipids) if patient randomised in standard monitoring arm;
- Glucose, and creatinine if patient under DTG and metformine and patient-centered monitoring arm.
- Urinary  $\beta$ -HCG in women of childbearing potential.

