#### **11.4.4 Interim analyses**

The DSMB will meet for a single interim safety analysis on the first 100 patients randomized once the end of the time window for their 24 weeks study visit is reached. The Sponsor-Investigator and all Study investigators will receive the related DSMB advice blinded to study arm. In addition to the scheduled meetings, extraordinary meetings may be requested by DSMB members, the Sponsor-Investigator, or the Study Scientific Committee at any time. The DSMB will review the safety data and may make recommendations about the conduct of the trial (study interruption) should any safety concerns be identified. The interim analysis will be prepared by an independent, unblinded statistician.

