| RCT, 48W switch study in experienced pts ( DOMONO )                                                    | N = 104 pts on cART for 40 months with CD4 nadir of 340; randomized to immediate switch to DTG monotherapy or deferred switch after 24W                                                                                                                                                                    | Confidential (see e-mail by [name] 21.1.20): when 77/96 on DTG monoT pts had reached W48 of monotherapy, VF had developed in 8 (2 before W24, 6 after W24) . This led to the premature study discontinuation. Although DTG monoT was non-inferior to cART at W24, VF continued to occur after W24 and led to DTG resistance in 3 . Final results at CROI 2017                                                                                                                                                     |                                                                                                                              |
| RCT in experienced pts with VL <50 cp/mL on current ART ( DOLAM )                                      | N = 450; randomized 1:1:1 to DTG, DTG + 3TC, or current treatment (control). Follow-up at BL, 4, 12, 24, 36, 48W.

Pts on stable triT with <50 cp/mL in ≥2 consecutive determinations for ≥12 months, no prior VF or resistance mutations to 3TC/FTC or INSTI, nadir CD4 >200cells/mm  . | Confidential (see e-mail by [name] on 9.2.2017): 2 VF in monoT arm at the end of phase A (90 pts, 24W follow-up). According to DSMB advise (called according to protocol safety rules “DSMB will review the data if the proportion of confirmed virological failure in any of the experimental arms reaches ≥5%”), the Steering Committee has decided to interrupt the DTG arm and to continue the DOLAM study with two arms: CONTROL and DTG+3TC (no safety issues in dualtherapy arm). Results expected after October 2017 |                                                                                                                              |

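### The automatic DSMB trigger for failures with new resistance lapses at the single week-24 interim, leaving roughly 44-67% of week 24-48 exposure without it

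*Protocol*

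**What the plan says.** Section 11.3 lists two situations in which the DSMB will be convened outside its planned meeting. The first is a count from the trial itself: "> 2 patients experienced virological failure and a new resistances on DTG + FTC dual therapy". It carries a time limit, since the failures must occur "on DTG + FTC dual therapy before the planned interim safety analysis is done". The second is new external data that speak against testing the dual-therapy arm.

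The interim that ends the first rule is defined in the same section: "a safety interim analysis on the first 100 patients randomized will be done once reached the end of the time window" of the week-24 visit. Section 11.4.4 confirms that there is only one: "The DSMB will meet for a single interim safety analysis".

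Three things continue after it. A report goes to the DSMB every 6 months (Section 11.3); it covers virological failures but does not name resistance and sets no threshold. DSMB members, the sponsor-investigator or the scientific committee may ask for an extraordinary meeting at any time (Section 11.4.4). The stopping rules in Section 11.3 also apply, but they give no number for failures or resistance.

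On timing, Section 3.4 says of the randomised dolutegravir monotherapy switch trial that "most of virological failures occurred after week 24 and led to INSTI-associated resistance mutations in three patients", although monotherapy had been non-inferior at week 24. Supplementary File SF1 gives the counts: "VF had developed in 8 (2 before W24, 6 after W24").

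**The concern.** Section 3.7 names virological failure on DTG + FTC as the main risk of the trial, and item (1) is the only rule that turns a number of resistant failures into an obligation to convene the DSMB. Its end point is tied to a look at week 24 of the first 100 patients. The randomised trial that the protocol cites on timing looked acceptable at week 24 and was stopped for failures that mostly came later.

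At stake is whether the third and later resistant failures, if they occur after the interim, lead to a DSMB review by rule or only because someone decides to ask for one. The protocol gives no reason for the time limit. SF1 and SF2 quote another trial's rule, a DSMB review once confirmed failures in any experimental arm reach 5%, and as quoted that rule has no end date.

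**Working it through.** The protocol gives no figure for exposure before and after the interim, so this is derived from its planning numbers.

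**Inputs.** Total N = 184 (Synopsis; Section 11.2). The N itself reproduces: (1.96 + 0.842)² × (0.97×0.03 + 0.94×0.06) / (0.12 − 0.03)² = 7.85 × 0.0855 / 0.0081 = 82.8, so 83 per group and 166 in total; 166 / 0.9 = 184.4. Recruitment: one year, May 2017 to June 2018 (Synopsis). Interim: patient 100 at week 24 plus the 7-day window (Sections 11.3 and 9.3.6). Follow-up: 48 weeks.

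**Assumptions.** Even accrual over A weeks, with A = 52 or 56.5 (the second for the stated months). No dropout. Delay d weeks between window closure and completion of the interim.

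**Calendar time at which the trigger lapses.** Patient 100 enters at A × 99.5/184.
- A = 52: 28.1 weeks, so T = 28.1 + 24 + 1 = 53.1 weeks.
- A = 56.5: 30.55 weeks, so T = 55.55 weeks.

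**Share of week 24-48 person-time accrued by T.** Patients who entered before T − 48 have completed this period. Those who entered in the next 24 weeks have on average completed half of it. Later entrants have none. The share is therefore (T − 48)/A + ½ × 24/A = (T − 36)/A.
- A = 52: (53.1 − 36)/52 = 0.329, so 67.1% falls after the trigger lapses.
- A = 56.5: (55.55 − 36)/56.5 = 0.346, so 65.4% falls after.

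With A = 52 and no delay, 81 of 184 patients have not yet passed week 24 and 18 have reached week 48.

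**Delay.** The trigger runs until the interim is done, so T becomes T + d.

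| d (weeks) | After lapse, A = 52 | After lapse, A = 56.5 |
|---|---|---|
| 0 | 67% | 65% |
| 4 | 59% | 58% |
| 8 | 52% | 51% |
| 12 | 44% | 44% |

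**Accrual pace.** With no delay, accrual over 26, 39 or 78 weeks gives 82%, 74% or 60%.

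**Evidence on timing.** 6/8 = 75% of failures came after week 24 in the cited monotherapy trial. The number is small: with an even split, 6 or more of 8 would occur with probability (28 + 8 + 1)/256 = 0.14. Section 3.4 describes the three observational monotherapy studies over 24 weeks, so they say little about later failures.

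**The case against.** The strongest reply is that oversight does not stop at the interim. The trial is open-label and HIV-RNA results reach investigators within a week (Section 11.3). Resistance testing is done in real time (Section 9.1). Safety signals must reach the sponsor-investigator within 24 hours (Section 10.1.2), and a DSMB meeting can be requested at any time (Section 11.4.4). A reader might infer that a late cluster would reach the DSMB only through a periodic summary, up to 6 months on. The documents do not support that; it would require every other route to go unused.

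A second reply is that the evidence on late failure is monotherapy. The dual-therapy data cited in Section 3.4 are reassuring: 101 of 104 patients suppressed at week 40 on DTG + 3TC, and all 38 at week 48 on DTG + rilpivirine. The one dual-therapy failure given a late time (weeks 36-48) was in first-line treatment and showed no resistance, so it would not have counted towards the trigger. It does not follow that resistant failures on DTG + FTC will come mostly after week 24.

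Third, the rule runs on calendar time. A reader might infer that it operates only while the event is least likely, but about a third of week 24-48 exposure, from the early enrollees, is covered even without delay. Over the whole 48 weeks, 44% of person-time falls after the lapse.

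Finally, the wording has a coherent purpose: it covers the time before the DSMB's first formal look, after which the DSMB may recommend modification or ask for meetings.

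All of this limits the consequence. None of it supplies an automatic count after the interim, or a reason why the count should end there.

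**Conclusion.** The point holds as a gap in the automatic trigger, not as a loss of oversight and not as a contradiction in the protocol. After the interim no number of resistant failures on DTG + FTC obliges a DSMB review. The uncovered share of week 24-48 person-time is about 65-67% if the interim is immediate, and about 44-59% if it is completed 4 to 12 weeks later. These figures assume even accrual of 184 patients over 12 to 13 months and no dropout.

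The mismatch with the protocol's evidence on timing rests on 8 failures in one monotherapy trial. It is a reason for caution and does not predict when DTG + FTC would fail. This is a cheap improvement that should be made; the trial's validity does not depend on it.

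**What to change.** In Section 11.3 (1), replace the time limit that closes the sentence with: *at any time until the last participant's week-48 visit, counted cumulatively from the first randomisation*. Leave the numerical threshold and the DSMB's freedom of recommendation as they are. If the sponsor prefers to keep the present limit, the section should say why the trigger ends at the interim.

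The change is one phrase in the protocol or DSMB charter. It needs no extra data or patients, since failures and resistance results are already collected to week 48. The downside is possibly one extra DSMB meeting.
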